## Abstract

**Background:**

The use of education alone as a technique to change behavior in interventions is usually insufficient, particularly in health interventions. Behavior change techniques have been shown to be effective in fostering positive changes in health behaviors such as diet and physical activity. The upskilling of health professionals can increase perceived capability and motivation toward eliciting change in clients’ behaviors. However, to date, dietitians have received limited training in behavior change and have expressed a need for continuous professional development.

**Objective:**

The study objectives are to (1) develop and evaluate the effectiveness and acceptability of two 2-hour behavior change workshops on changing dietitians behavior (ie, range of behavior change techniques used and frequency of use) across 3 time points; (2) determine if participation in these workshops will elicit changes in dietitians’ perceived capability, opportunity, and motivation toward using behavior change techniques; and (3) determine the acceptability of the training and its application in practice by dietitians.

**Methods:**

We will recruit registered dietitians (N=140) in Australia to participate in this randomized controlled trial. Participants will be randomly assigned to either the intervention or 3-month waitlist control condition and complete outcome measures at 3 time points: baseline, after the workshop, and follow-up at 3 months. Both groups will complete 2 workshops on behavior change that are guided by the COM-B (Capability, Opportunity, Motivation, and Behavior) Model and embedded with behavior change techniques. The primary outcome is changes in behavior, (ie, the range of behavior change techniques used and their frequency of use). Secondary outcomes include changes in perceived capability, opportunity, motivation, and preparedness as a health professional toward delivering behavior change techniques. The acceptability of the workshops will also be assessed after the workshop through the postworkshop survey and semistructured interviews. A series of 2-way repeated measures ANOVAs and regressions will be used. Qualitative data will be analyzed using thematic analysis.

**Results:**

Participant recruitment commenced in June 2023. The results of the study are expected to be published in November 2024. The results will allow us to assess comparisons between the intervention and waitlist control groups, as well as changes in perceived capability, opportunity, motivation, and preparedness over a 3-month period. It will also provide an understanding of the acceptability of the training as a form of continuous professional development for dietitians.

**Conclusions:**

If found to be effective, the results of this 2-arm randomized controlled trial will guide future training and continuous professional development for health professionals in changing behavior in practice. Our findings will contribute to our understanding of the application of behavior change techniques in practice with clients and identify components of COM-B where dietitians may need future support.

**Trial Registration:**

ACTRN12623000525684; https://www.anzctr.org.au/ACTRN12623000525684.aspx

**International Registered Report Identifier (IRRID):**

PRR1-10.2196/49723

## Introduction

Chronic diseases such as cardiovascular disease, chronic obstructive pulmonary disease, cancer, and diabetes are among the most common noncommunicable diseases, which contribute to the burden of disease in Australia [1]. Approximately 38% of this burden of disease could be prevented by addressing behavioral determinants of disease such as overweight (including obesity) and dietary risk behaviors [2]. The majority of Australians do not meet the Australian government dietary guidelines for fruit and vegetable consumption, with almost 50% of adults eating fewer than 2 serves of fruit and 92% not eating the recommended 5 serves of vegetables daily [3]. Therefore, there is a need for behavior change interventions and health promotion across primary health care settings. However, while health professionals typically focus on education for clients, consumers, or patients (from here forward, any patient, client, or consumer will be referred to as clients), this is usually insufficient for facilitating behavior change and leads to missed opportunities in practice [4]. Behavior change techniques, which are considered the “active ingredients” of intervention design, have been shown to be more effective in improving client outcomes compared to those without, particularly in dietary interventions [5,6]. As such, it is important that health professionals are equipped with the capability and motivation to effectively facilitate behavior change among clients.

Brief opportunistic interventions in routine consultations have been effective for eliciting change in clients’ behavior [7,8]. However, health care professionals report barriers to the implementation of behavior change techniques, such as poor confidence in individual skills and knowledge of behavior change, time constraints, priorities, and access to sufficient training [4]. Dietitians engaging in both in-person and telehealth consultations are in an optimal role where they can reach both metropolitan and rural clients to deliver health-behavior change interventions [9]. Additionally, many dietitians have expressed an unmet need for knowledge and skills in behavior change [10,11].

The understanding of behavior change theories and techniques can help health professionals understand behavior and the mechanisms that elicit or facilitate behavior change [12]. Theoretical models, such as the COM-B (Capability, Opportunity, Motivation, and Behavior) model [13] can provide a framework for identifying and explaining the factors enabling or hindering changes in behavior, which can guide intervention design for effective behavior change [14]. The COM-B model posits that an individual’s capability (ie, physical and psychological capability), opportunity (ie, social and physical opportunity), and motivation (ie, reflective and automatic) interact in a bidirectional way and can explain behavior [14]. As such, interventions informed by these constructs have been effective in eliciting changes in knowledge and behavior [15,16], alongside the use of behavior change techniques [17,18]. Behavior change techniques can be considered the individual units or “active ingredients” that target components of behavior that need to change [6]. These components or units that form interventions can help us identify the parts of the intervention that work or do not work, providing valuable information for operationalizing effective intervention designs. The use of behavior change techniques can be effective in both changing the behavior of clients and health professionals [19,20]. For example, behavior change techniques such as goal setting, action planning, and self-monitoring have elicited behavior change in physical activity and food-related behaviors [21-24].

Despite the capacity of health professionals to foster behavior change in clients using behavior change techniques, no such training is consistently delivered to dietitians, particularly in formalized education [25]. Currently, the use of behavior change techniques used in dietary practice and dietary-based interventions is based around goal setting, problem-solving, social support, self-monitoring, and education-based techniques (eg, instructions on behavior and credible sources), which are consistent throughout the literature [5,26,27]. Therefore, the primary aim of the study is to develop and evaluate the effectiveness and acceptability of two 2-hour behavior change workshops on changing dietitians’ behavior, that is, changes in the number and frequency of behavior change techniques dietitians use in practice. It is anticipated that the workshops will prompt dietitians to use a larger variety and frequency of using these techniques in practice between baseline, after the workshop, and 3-month follow-up. A secondary aim is to determine if attendance at these workshops will demonstrate an increase in dietitians’ capability, opportunity, and motivation toward using these techniques. In these workshops, the use of behavior change techniques will underlie workshop material to target dietitians’ barriers across capability (eg, persuasion around capability), opportunity (eg, identifying barriers and problem-solving), and motivation (eg, focus on past success). Therefore, we hypothesize that engagement in these workshops will predict dietitians’ capability, perceived opportunity, and motivation toward using behavior change techniques from baseline and after the workshop to 3-month follow-up. Lastly, we also aim to determine the acceptability of the training.

## Methods

### Study Design and Procedure

This study is a 2-arm randomized controlled trial with a 3-month follow-up. Participants will complete a questionnaire at baseline, immediately after the intervention, and 3 months after the intervention. Participants will express their interest to participate in the study through a Qualtrics survey. Informed consent will be obtained at the start of this survey. Following this initial survey, dietitians will be randomized in blocks of 4 into either the intervention or a waitlist control condition (1:1). Block randomization will be conducted with allocation concealment from the active research team through the use of sealed, opaque envelopes. Emails will be sent to participants with the initial baseline questionnaire, and they will be informed if they can participate in the workshops immediately or if their available workshop will be in 3 months. Once dietitians have been randomized and received their baseline questionnaire, they have been enrolled in the study as participants. Both groups will participate in both workshops and complete a questionnaire immediately after participation in the second workshop and at the 3-month follow-up. The waitlist control group will be debriefed after the final questionnaire regarding their allocation to the waitlist control group. Postworkshop data collected from the waitlist control group will also be included in the final data set. Figure 1 shows a flowchart for each group’s progression in the trial. This protocol will adhere to the CONSORT (Consolidated Standards of Reporting Trials) and SPIRIT (Standard Protocol Items: Recommendations for Interventional Trials) guidelines for randomized controlled trials [28].

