### Data Collection Methods

Once an expression of interest has been received through the Qualtrics survey, the participant will be asked to complete an initial baseline measure. In this baseline questionnaire, participants will be asked questions on their demographics (eg, age, gender, and highest level of qualification), current perceived knowledge and behavior (ie, use of behavior change techniques), the COM-B questionnaire [38], and preparedness as a health professional to deliver behavior change techniques. The same assessments (excluding demographics) will be repeated at the postworkshop and follow-up time points. At the postworkshop time point, the questionnaire will also include items on the acceptability of the workshops.

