### Measures

Behavior will be measured with two items to determine (1) the use of behavior change techniques and (2) the frequency of use. The first item asks participants “Which of the following behavior change techniques do you use in practice?” Participants will indicate which of the 14 techniques they have used by rating their answer as either yes, no, or unsure. A total of 14 techniques were chosen based upon techniques used for dietary behavior change in the literature [31], as well as consultations with an advisory group of dietitians to determine the appropriateness and practicality of the techniques. A composite score will be calculated to determine the number of techniques used. A second item will also be included to identify how frequently dietitians use these techniques in practice, for example, “How often do you currently use behavior change techniques when interacting with clients?” Participants will rate this item on a 5-point Likert scale from never (0) to always (4).

Capability, opportunity, and motivation will be measured using the COM-B questionnaire [38], which has been adapted for delivering behavior change techniques when interacting with clients in health contexts. This measure includes 6 items and 6 domains that reflect each component of the COM-B model as outlined by Michie et al [13]. Participants will rate their level of agreement with each item on an 11-point scale, with items ranging from strongly disagree (0) to strongly agree (10). An example item includes “I have the PHYSICAL opportunity to deliver behavior change techniques when interacting with clients (eg, time, the necessary materials, reminders, and space).”

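### Baseline is self-reported after randomisation, and nothing stops participants from knowing their workshop timing, and so in substance their arm, when they answer

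*Protocol article*

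**What the plan says.** Study Design and Procedure (protocol article, Methods) sets the order. Dietitians complete an expression-of-interest survey with consent and are then randomised 1:1 in blocks of 4. After that, "Emails will be sent to participants with the initial baseline questionnaire, and they will be informed if they can participate in the workshops immediately". The other arm's notice is of a delayed start, worded "or if their available workshop will be in 3 months". Enrolment is defined in the same order: "Once dietitians have been randomized and received their baseline questionnaire, they have been enrolled in the study as participants". It requires receipt of the questionnaire, not its return.

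Two further sentences in that section bear on who knows what. Concealment is directed at the study staff: "Block randomization will be conducted with allocation concealment from the active research team through the use of sealed, opaque envelopes". And "The waitlist control group will be debriefed after the final questionnaire regarding their allocation to the waitlist control group".

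Data Collection Methods says: "Once an expression of interest has been received through the Qualtrics survey, the participant will be asked to complete an initial baseline measure". It does not mention randomisation or disclosure of timing. It also shows that demographics are collected in the baseline questionnaire.

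Under Measures, the outcomes are self-ratings. For the first primary outcome, "Participants will indicate which of the 14 techniques they have used by rating their answer as either yes, no, or unsure". The second is a single frequency item scored 0 to 4. Capability, opportunity, motivation and preparedness are agreement ratings.

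Under Primary and Secondary Outcomes, the arm comparison is a two-way repeated measures ANOVA of group by the three time points, baseline being the first, with demographic covariates.

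**The concern.** A baseline is useful in a randomised comparison because allocation cannot have influenced it. Here it can. A dietitian about to start training and one told to wait 3 months may rate their current use of techniques, confidence or motivation differently. The answers are subjective, so there is room for that. If baseline moves in one arm, the apparent change in that arm moves by the same amount, and the group-by-time interaction cannot tell this from a workshop effect. The error could favour the workshops or hide a real benefit.

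The second route is loss. People told to wait may be less willing to return the questionnaire. They count as enrolled but have no baseline, and the numbers can differ by arm. This matters in a trial that already allows for 50% attrition.

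**Working it through.** **1. Order of events.** Study Design and Procedure gives survey and consent, then randomisation, then the baseline questionnaire with notice of workshop timing. The enrolment definition confirms that the questionnaire arrives after randomisation. Data Collection Methods places baseline after the expression of interest, which fits the same order and does not put it before randomisation. No section requires the questionnaire back before timing is disclosed.

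**2. Does timing identify the arm?** There are two arms, both receive the two workshops, and they differ in start. One start is immediate and the other is 3 months later. Knowing the start therefore amounts to knowing the arm.

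**3. How a baseline shift enters the comparison.** The plan states no figure for this, so there is none to reproduce. The following is an illustration.

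Inputs from the document: 84 analysed (42 per arm), the stated requirement; and 140 × (1 − 0.5) = 70 analysed (35 per arm), the recruitment target after the stated attrition allowance. Inputs assumed: shift s of 0.1, 0.2 or 0.3 SD in one arm's baseline, correlation ρ = 0.5 between time points, no true effect, normal approximation.

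- Bias in the between-arm difference in change = s (in absolute value).
- SE = √(2(1 − ρ)) × √(2/n). With ρ = 0.5 the first factor is 1. For n = 42, SE = √(2/42) = 0.218; for n = 35, SE = √(2/35) = 0.239.
- Type I error = 1 − Φ(1.96 − s/SE) + Φ(−1.96 − s/SE).

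Example, s = 0.2 and n = 42: s/SE = 0.2/0.218 = 0.917, so 1 − Φ(1.043) + Φ(−2.877) = 0.148 + 0.002 = 0.150.

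| Assumed shift (SD) | 84 analysed | 70 analysed |
|---|---|---|
| 0.1 | 7.4% | 7.0% |
| 0.2 | 15.0% | 13.3% |
| 0.3 | 28.0% | 24.1% |

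**4. Is this an artefact of using a change score?** The planned test is the three-time-point interaction. Under compound symmetry with the shift at baseline only, its noncentrality is λ = s² × (2/3) / ((1 − ρ) × 2/n). For s = 0.2 and n = 42 this is 0.04 × 0.667 / (0.5 × 0.0476) = 1.12. With 2 and 164 degrees of freedom the rejection rate is 14.2%, against 15.0% above. With 0.1 and 0.3 SD it is 7.1% and 27.1%. The conclusion does not depend on the simplification.

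**5. Missing baselines.** Preliminary Analyses deletes cases with more than 40% missing but does not say over what the percentage is counted. If it is counted over three questionnaires of similar length, a missing baseline alone is 1/3 = 33%, below the limit; baseline plus one other is 2/3 = 67%, above it. Even below the limit, a repeated measures ANOVA needs all three time points unless values are imputed. Unequal return by arm can therefore become unequal removal.

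**The case against.** Several points on the other side are fair.

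- **One email is not stated outright.** The text has emails in the plural, and the clause about timing names no channel. Figure 1, which charts each group's progression, is not available here. One mailing is the natural reading, but only a reading. The point needs less: that timing can be known before baseline is returned, and nothing prevents this.
- **The arm may not be named.** A reader might infer that the email tells people they are waitlist controls. The end-of-study debrief suggests that the label is withheld, and with staggered recruitment a later date might pass as scheduling. That qualifies the point, but the delay still identifies the arm in substance and may affect answers whatever it is called.
- **Some protection is planned.** Enrolment on receipt keeps non-returners in the enrolled set, and the plan names intention-to-treat analysis, a dropout comparison and possible multiple imputation. None of these corrects a shifted answer. For someone who never returned baseline they also have little to work with, because demographics are in that same questionnaire. The planned chi-square test at baseline cannot separate chance imbalance from an allocation effect and corrects neither.
- **The regressions are not affected in the same way.** It is tempting to say that the bias also enters the arm effect through the regressions that control for baseline behaviour. Those regressions relate changes in capability, opportunity, motivation and preparedness to changes in behaviour, and no arm term is stated. Only the group-by-time ANOVA carries the arm comparison.
- **The size is assumed.** Neither the shift nor the correlation comes from the document. Larger error rates follow if all 140 are analysed, but that requires no attrition, contrary to the plan's own allowance.

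**Conclusion.** The point holds as a weakness of the stated procedure. Baseline follows randomisation, may be answered with the workshop timing known, is wholly self-reported for the outcomes, and is the first level of the repeated factor in the arm comparison. The baseline-adjusted arm comparison that would dampen the bias is not the one the protocol states.

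The document does not show that baseline answers will differ by arm, in which direction, or by how much. A reader might conclude that the trial is biased towards the workshops; the text supports only that it is open to bias either way. If the shift is 0.1 to 0.3 SD, with correlation 0.5 and no true effect, a nominal 5% change comparison rejects about 7% to 28% of the time with 84 analysed and about 7% to 24% with 70. If there is no shift and return does not differ by arm, there is no harm.

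Confidence is high on the order of events, and moderate that timing is disclosed in the same mailing and that the effect would be material.

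**What to change.** **Further participants.** Place the baseline questionnaire inside the expression-of-interest and consent survey, or otherwise collect it before randomisation. Randomise only after it is submitted, and send workshop timing afterwards. Keep everyone randomised in the intention-to-treat analysis. Align Study Design and Procedure and Data Collection Methods so that both state this order.

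**Participants already enrolled under the present order** (recruitment began in June 2023). Report, by arm, the number randomised and the number who returned baseline. Add a sensitivity analysis that compares the arms at the postworkshop and follow-up time points without the self-reported baseline, or one that compares results for those enrolled before and after the change. Recording when each questionnaire was completed relative to the allocation notice would not help if both arrived together, since every answer would then follow disclosure. Excluding all earlier participants could remove much of the sample.

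**Cost.** An amendment, a change to the survey, and a reordering of messages. A longer first survey may lose some sign-ups, but those losses come before randomisation and so do not bias the comparison between arms. For those already enrolled, no analysis can restore an unaffected baseline, so the change is worth more the earlier it is made.

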**Figure 1 figure1:**
[figure not shown]
Outline of the trial.

### Participants

Participants will be dietitians who are currently working in Australia and hold full membership with Dietitians Australia. Participants will be recruited using purposive sampling, through both social media advertisements and newsletters directed through nutrition and dietetic organizations, and through snowballing. Recruitment of participants will be staggered over a 12-month period. A similar intervention in behavior change for health professionals found medium to large effect sizes for changes in mechanisms of change (eg, perceived knowledge) [16]. Therefore, anticipating medium to large effect sizes, a-priori analysis was conducted in G power (Axel Buchner; *F*_1,82_=0.2; power =.80; α=.05) indicating that 42 participants in each group would be adequate [29]. This means a total sample size of 84. It is anticipated that there may be high attrition in this study. Therefore, we aim to recruit approximately 140 participants to ensure that if 50% of each group are lost to attrition, the proposed analysis will be sufficiently powered. This dropout rate of 50% is conservative given that similar interventions in training health professionals can report moderate (20%) to high (50%) attrition rates [20,30].

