#### Primary and Secondary Outcomes

The primary and secondary outcome variables will be assessed at the baseline, postworkshop, and follow-up time points. A chi-square test will be used to assess if there are any differences between the intervention group and waitlist control at baseline. A 2-way repeated measures ANOVA will be conducted to compare the means between the intervention group and waitlist control group (between-subjects factor) over the 3 time points (within-subjects factor) for each of the primary and secondary variables. This analysis will be run to test for any time through conditional interactions. Demographics, such as age, gender, role of dietitian, and consultation delivery mode, will be included as covariates in the analysis. Multiple regression analyses will be used to determine whether changes (residual) in capability, opportunity, motivation, and health professional preparedness predict changes in behavior (range of use or frequency of use) at each of the 3 time points (while controlling for baseline behavior).

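### At the 50% attrition it says it covers, recruiting 140 leaves 70 participants, 14 below the protocol's own requirement of 84

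*Protocol article*

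**What the plan says.** All the figures stand in one paragraph of the protocol article, under Participants.

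- **Requirement.** The power calculation ("power =.80; α=.05") is reported as "indicating that 42 participants in each group would be adequate". The text adds: "This means a total sample size of 84".
- **Inflation for attrition.** The plan is to "recruit approximately 140 participants to ensure that if 50% of each group are lost to attrition, the proposed analysis will be sufficiently powered".
- **Rate repeated.** The next sentence reads: "This dropout rate of 50% is conservative given that similar interventions in training health professionals can report moderate (20%) to high (50%) attrition rates".

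The Methods part of the abstract carries the same target: "We will recruit registered dietitians (N=140) in Australia to participate in this randomized controlled trial". The analysis that the sample must support, under Primary and Secondary Outcomes, is: "A 2-way repeated measures ANOVA will be conducted to compare the means between the intervention group and waitlist control group", over three time points.

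**The concern.** A recruitment target inflated for dropout should return the required number once the stated dropout is removed. Here it does not, and the mismatch involves only the protocol's own figures.

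This matters because the authors expect attrition to be high, and 50% is the upper end of the range they cite. Under Strengths and Limitations they also warn that motivated volunteers may show little or no change. A null result after heavy dropout is therefore foreseeable. A reader relying on the Participants section would take such a result as coming from a trial that still met its planned size, when it would not have.

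**Working it through.** **Inputs (protocol article)**

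- Required number: 42 per group, 84 in total (Participants)
- Recruitment target: about 140 (Participants; abstract)
- Attrition to be absorbed: 50% of each group (Participants)
- Power 0.80, alpha 0.05 (Participants)
- Allocation 1:1 (Study Design and Procedure)

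**Step 1. Try to reproduce 140.** With required number N and dropout d, the recruitment target is N/(1 − d).

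- d = 0.50: 84/0.50 = 168
- d = 0.40: 84/0.60 = 140
- Common mistaken form N × (1 + d), with d = 0.50: 84 × 1.5 = 126

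So 140 is exactly the target for 40% attrition. Neither the correct nor the mistaken formula gives it at 50%.

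**Step 2. What 140 leaves at 50%.** 140 × 0.50 = 70, or 35 per group. The shortfall is 84 − 70 = 14, or 7 per group.

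**Step 3. Attrition that 140 can absorb.** 1 − 84/140 = 0.40. The gap to the target for 50% is 168 − 140 = 28 recruits, and 28/168 = 16.7%.

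**Step 4. What the shortfall means for power, on a stated condition.** Suppose that 84 gives exactly 80% power at alpha 0.05. Solve for the noncentrality at 84, scale it by 70/84, and read off power from the noncentral F distribution.

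- Group comparison: noncentrality 8.04 at df 1, 82. Then 8.04 × 70/84 = 6.70 at df 1, 68, giving 72.3% power.
- Group-by-time interaction, three time points: noncentrality 9.81 at df 2, 164. Then 9.81 × 70/84 = 8.18 at df 2, 136, giving 71.7% power.

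**Step 5. Can that condition be checked?** No. The effect is printed as an F value of 0.2 with df 1 and 82. Neither the test nor the within-person correlation is given. Taking 0.2 to be Cohen's f, with three time points (m = 3) and correlation ρ = 0.5 (all assumptions), the noncentrality is f²Nm/(1 + (m − 1)ρ) for the between-groups effect and f²Nm/(1 − ρ) for the interaction.

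| Effect tested | Power at N = 84 | Power at N = 70 |
|---|---|---|
| Between groups | 60% | 52% |
| Group-by-time interaction | 98% | 96% |

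With correlation 0 instead, the interaction at N = 70 has about 73% power, and 82 participants would be needed for 80%. Several assumption sets come close to 84, but the document does not say which one was used.

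**The case against.** The strongest reply is that being below 84 is not the same as being underpowered. A reader might infer from the shortfall that the sufficient-power claim is false in fact, or that the trial would have 72% power at 50% loss. The document supports neither inference. On one plausible set of inputs, 70 participants give about 96% power for the interaction; on another they give about 52% for the group effect. This part of the reply stands, and it limits the point to a comparison with the protocol's own requirement.

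Other replies carry less weight.

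- **Rounding.** The target is approximate, but that cannot cover a gap of 28 recruits.
- **A slip in the rate.** The 50% is repeated in the next sentence and defended as conservative. A 40% attrition rate appears nowhere.
- **Intention-to-treat analysis and imputation.** Preliminary Analyses plans the former and allows the latter, so not everyone lost need leave every analysis. But imputation is only to be considered where appropriate, and cases with more than 40% missing are deleted. The step from 84 to 140 also makes sense only if lost participants do not count.
- **Limited reach.** The shortfall arises only above 40% loss, the upper third of the cited 20% to 50% range. At 20% loss, 140 × 0.80 = 112 remain. This is true, but 50% is the case the sentence claims to cover.

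**Conclusion.** The point holds as an arithmetic contradiction within the Participants section. At 50% attrition, 140 recruits leave 70, which is 14 below the required 84. The target of 140 protects 84 up to 40% attrition, and 168 would be needed at 50%. This rests on the protocol's figures alone, with equal allocation and equal loss in the two groups, as the text itself supposes.

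The loss of power, from 80% to about 72%, rests on one further assumption: that 84 gives exactly 80%. The printed inputs do not establish that, so the figure illustrates the size of the shortfall and is not the trial's power. An unsupported statement about protection against attrition should be corrected, but nothing here shows the design to be unworkable.

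**What to change.** Keep 140 and replace the attrition sentence, for example with:

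> A target of 140 recruits retains the required 84 if attrition is no more than 40%; at 50% attrition 70 remain, below the required 84 (about 72% power if 84 gives exactly 80%).

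The bracket may be left out, but the 72% should not appear without its condition. The following sentence, which calls 50% the conservative planning rate, needs to be brought into line. If protection against 50% loss is to be claimed, the target to state is 168, here and in the abstract. It would also help to state the test, the effect measure and the within-person correlation behind the 84, so that power at any retained number can be checked.

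Keeping 140 costs a small edit and a somewhat less favourable claim, with no change to design or analysis. Choosing 168 costs 28 more recruits.
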